### 5.7.2 Analysis

Primary analysis: We will compare HTC uptake between the study groups. We hypothesize that HTC uptake among men offered lottery and loss aversion incentives will be higher than uptake among men offered fixed incentives. We will test for significant differences in HTC uptake between the following groups using the 2-tailed  $\chi^2$  analysis or other appropriate statistical methods: a) lottery vs. fixed incentive; and b) loss aversion vs. fixed incentive. To further inform policies that use incentives to promote health behaviors, we will compare HTC uptake among those receiving lottery vs. loss aversion incentives. We also hypothesize that those offered larger incentives amounts will have higher HTC uptake.

Secondary analyses: (a) **HIV-infected men:** We will compare the proportion of HIV testers who are HIV-positive in each of the study groups using 2-tailed  $\chi^2$  tests or other appropriate statistical methods. Our hypothesis is that the lottery incentive arm will have a *larger* proportion of HIV-infected men than the other arms, on the basis that it will draw men who are less risk averse.

(b) **Risk preferences:** We will estimate logistic regression models, or other appropriate statistical models, with an interaction term between study group and the participant's risk preferences. Our hypothesis is that lottery-based incentives will be most effective for men with risk seeking preferences, while other incentives will be most effective for men with risk averse preferences.

Analysis of qualitative data: Translated data will be imported into a qualitative analysis software program, for textual analysis [56] guided by grounded theoretical approaches [55], in which research team members iteratively analyze transcripts and develop a common set of codes describing patterns observed in the data. New codes proposed by research team members will be vetted and defined in relation to existing codes. As new data are collected and reviewed, and data reach analytic saturation, the research team members will independently code the interviews and discuss data segments that are particularly rich or difficult to code. Team members will discuss and resolve divergent coding and interpretations of findings to ensure that codes are applied consistently. Analytical memos will extract and summarize findings following the domains of inquiry outlined above, in order to extract themes and central ideas that explain the meaning of the data.

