**HIV testing and treatment utilization are health behaviors ideally suited for incentive-based interventions.** The immediate “costs” of testing, for example, include not just transport costs but also psychosocial ones such as stigma and fear of testing HIV-positive or disclosure [30-33]. The benefits of testing, on the other hand, are more in the future and include the prospect of ART if one tests HIV positive. *Incentives are ideal in this case because they create immediate benefits to testing and even offset some immediate costs. However, the standard approach of offering fixed incentives does not fully achieve desired behaviors and fails to realize the entire potential of incentives by not incorporating ideas from behavioral economics.* For some, small incentives may be overlooked due to the “*peanuts effect*” (rewards may be “small peanuts”, not worth the effort) [9], a phenomenon supported by our pilot data [28]. Behavioral economics suggests novel approaches that may be *more effective*, and *less costly*.

**Lotteries may be more effective in promoting HIV testing than small, fixed incentives.** In seminal research, Kahneman and Tversky’s *Prospect Theory* showed that people place a greater decision weight on

probabilities near zero [8]. Thus lotteries with low probabilities of winning large prizes may be more appealing than a fixed incentive that is equal in its *mathematical* expected value. Lottery-based incentives may also be more effective because people tend to pay considerable attention to the *magnitude* of rewards [8, 34]. The *anticipated emotion* of winning a prize can be influential in driving behavior [34]. Lottery-based incentives may be ideal for implementing *targeted testing* and promoting HIV testing among higher risk men. Economists have shown that individuals' **risk preferences** (i.e. attitudes towards risk) are an important predictor of their interest in lotteries [35, 36], with individuals displaying "risk seeking" preferences having the most interest. Such preferences have been associated with health behaviors such as use of preventive medical care and cigarette smoking [37-39]. The men in our study who find lottery-based incentives *most* appealing may be those with risk seeking preferences, a group likely to include HIV-infected persons and those engaged in high risk behaviors.

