### 5.2 Randomization

We will compare two theoretically motivated incentive interventions to a standard, fixed incentive intervention. Each intervention will seek to encourage HTC uptake at testing venues in the community (described below).

The incentive interventions will have up to three different values in order to inform researchers and policymakers about the optimal incentive size. The *expected value* of each incentive intervention, within each tier of incentive value, will be the same so that we can draw unambiguous conclusions about the reasons why some incentive interventions work better than others. We will select up to three tiers of incentive value (e.g. low, medium and higher value incentive values), with the specific amounts of expected values per person in US dollars for the incentives determined during pre-enrollment community advisory board meetings. The expected value of the *highest* tier of incentive value will not exceed \$10/person, an amount that resembles

what has been used in some other studies in the region [27, 51], and that also corresponds to the sum of transport costs and the opportunity costs of time for some segments of the population.

Study participants will be randomized in equal ratios to the three incentive strategies and to up to three tiers of incentive value, as described below. Randomization will be performed with computer-generated assignments that are grouped in blocks so as to ensure roughly equal sizes in each study group.

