### 5.7.3 Sample Size & Accrual

The trial will have about 3,000 total participants. About 1,000 participants will be randomized to each type of incentive strategy (fixed incentives, lottery-based incentives, loss aversion incentives). There will also be equal numbers of participants assigned to each of the incentive amounts that are chosen. The sample size has been chosen to ensure there is adequate power for the primary *and* secondary analyses. For the primary analyses, if we assume HTC uptake is as low as 30% with fixed incentives, the study will have >80% power to detect a difference ( $\alpha=0.05$ , two-sided) in HTC uptake as small as 6% between the novel incentive and fixed incentive groups. If HTC uptake is 40% with fixed incentives, the study will have >80% power to detect a difference in HTC uptake as small as 7% in each of the novel incentive arms. For secondary analyses, if we assume 40% HTC uptake with fixed incentives (N=400), and 50% with lottery (N=500), we will have >80% power to detect a difference of at least 6% in HIV prevalence between testers in novel and fixed incentive groups (assuming prevalence of 6% in the fixed incentive group).

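### Aim 1 randomises incentive value as well as strategy, but the named primary test does not use the value tier and no test is named for the amount hypothesis

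*Protocol*

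**What the plan says.** Protocol 5.2 (Randomization) sets up two randomised factors: "Study participants will be randomized in equal ratios to the three incentive strategies and to up to three tiers of incentive value". The tiers have a stated purpose, "in order to inform researchers and policymakers about the optimal incentive size". Expected value is matched across strategies at each level: the expected value "of each incentive intervention, within each tier of incentive value, will be the same so that we can draw unambiguous conclusions" about why some interventions outperform others. The number of tiers and the amounts are still to be chosen.

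Protocol 5.7.2 (Analysis, Aim 1) gives the primary contrasts: "We will test for significant differences in HTC uptake between the following groups using the 2-tailed" chi-square, with other suitable methods allowed, for lottery vs fixed and for loss aversion vs fixed. A lottery vs loss aversion comparison is added to inform policy. The primary-analysis paragraph then ends: "We also hypothesize that those offered larger incentives amounts will have higher HTC uptake". No contrast, test or model is attached to that last statement. By contrast, secondary analysis (b) in the same section does specify a model with an interaction between study group and risk preferences.

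Protocol 5.7.3 (Sample Size & Accrual) sizes the trial on strategy: "About 1,000 participants will be randomized to each type of incentive strategy", with equal numbers at each amount. It states >80% power for 30% vs 36% and for 40% vs 47%, and gives no power for the amount comparison.

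**The concern.** The trial randomises a factor, says why, and predicts the direction of its effect. It then names primary tests that leave the factor out, and no test for the prediction itself. There are two consequences.

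- **Strategy contrasts.** If uptake rises with value, the uptake variance within a whole strategy arm includes between-tier variation. A crude two-proportion test counts that variation as noise. Its standard error is then slightly too large and the test slightly conservative. A tier-stratified test removes this at no cost.
- **Amount hypothesis.** The tiers exist to inform incentive size, and the hypothesis is directional and ordered. With no test named, the choice between an ordered trend, an unordered comparison and selected pairs can be made after the data are seen. An unordered test also discards the ordering that the protocol itself predicts.

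**Working it through.** **Inputs from the protocol.** About 1,000 men per strategy; equal numbers per amount; two-sided α = 0.05; 30% vs 36% and 40% vs 47% (5.7.3). With three tiers there are about 1,000/3 ≈ 333 men per strategy-by-tier cell, and about 3,000/3 = 1,000 men per tier.

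**Assumed, because the protocol gives no uptake by tier.** Tier uptake = mean − s, mean, mean + s, with s = 5, 10 or 15 points and the same risk difference in every tier.

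**Step 1: the stated power.** Power = Φ[(d − 1.96·SE0)/SE1], where SE0 = √(2·p̄(1−p̄)/n) and SE1 = √([p1(1−p1) + p2(1−p2)]/n).

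- 30% vs 36%, n = 1,000: SE0 = √(2×0.33×0.67/1000) = 0.02103; SE1 = √((0.2100+0.2304)/1000) = 0.02099. Power = Φ[(0.06 − 0.04122)/0.02099] = Φ(0.895) = **81.5%**. For 80% power 963 per arm are needed (996 with continuity correction).
- 40% vs 47%: power **88.5%** (787 per arm; 815 with correction).

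Both stated figures are met by the unstratified test.

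**Step 2: stratifying the strategy contrast by tier.** With equal tiers, p(1−p) in SE0 and SE1 is replaced by the mean of the tier-specific p_t(1−p_t). At 30% vs 36%, the variance of the risk difference falls to 0.992, 0.970 and 0.932 of the pooled value for s = 5, 10 and 15. A simulation (200,000 runs, 333 per cell) of the crude chi-square against the Cochran-Mantel-Haenszel (CMH) test gave:

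| Assumed spread s | 30% vs 36%: crude | CMH | 40% vs 47%: crude | CMH |
|---|---|---|---|---|
| 5 points | 81.5% | 81.7% | 88.4% | 88.5% |
| 10 points | 81.7% | 82.5% | 88.7% | 89.4% |
| 15 points | 82.4% | 84.2% | 89.2% | 90.3% |

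The gain is about 0 to 2 points. Under no strategy effect (30% in both arms), crude type I error is 5.0% at s = 0, 4.7% at s = 10 and 4.1% at s = 15. The CMH test stays at about 5%.

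**Step 3: the amount hypothesis.** Assume 30/33/36% across three tiers, with 1,000 men per tier. Noncentrality λ = n·Σ(p_t − p̄)²/[p̄(1−p̄)] = 1000×(0.0009 + 0 + 0.0009)/0.2211 = 8.14. The differences are linear in tier, so all of λ falls on the trend.

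- 1-df trend test: power **81%**.
- 2-df unordered chi-square: power **73%**.

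Using the hypothesised order is worth about 8 points.

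**Step 4: what within-tier tests can carry.** The Step 1 formula with 333 per cell gives 38% power (30% vs 36%) and 44% (40% vs 47%). The detectable difference at 80% power is about 10.4 to 10.8 points. With two tiers (500 per cell) power is 52% and 61%.

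**The case against.** The strongest reply is that little is broken. The sentence on the chi-square also admits other suitable methods, so a stratified test is already allowed, and strata and covariates are often settled in an analysis plan that is not at hand. Equal allocation and matched expected value give every strategy arm the same mix of values, so the pooled contrast is an unconfounded main effect of strategy. The trial is sized for that contrast and has the power claimed. The precision lost is small and rests on assumed tier spreads.

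Most of this stands, and it sets the size of the point. It does not remove it: the wording permits use of the tier without committing to it, and the amount hypothesis sits in the primary-analysis paragraph with no test.

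Two stronger readings are tempting, and the protocol supports neither.

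- **A reader might infer that the design was built for within-tier comparison,** since expected value is matched "within each tier of incentive value, will be the same so that we can draw unambiguous conclusions". But the Aim 1 hypotheses in section 2 are stated by strategy, section 5.7.3 powers about 1,000 per strategy, and within-tier tests have only 38–44% power at the planned differences.
- **A reader might infer that pooling hides an effect confined to one tier and that stratifying would recover it.** Section 1.2 says "For some, small incentives may be overlooked due to the" peanuts effect, but this is general motivation; no strategy-by-tier hypothesis follows. In a constructed case (fixed uptake 20/30/40%, lottery +12 points in the lowest tier only) the average difference is 12/3 = 4 points. Pooled power is 48% and CMH power 49%, because both test an average. The single-tier comparison would have 94%, but only if the right tier were singled out.

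**Conclusion.** The point holds as a modest improvement in method. The strategy-only primary test is valid and adequately powered, but it ignores a randomised factor that the protocol expects to predict uptake, and the ordered amount hypothesis has no named test. The gain is about 0 to 2 power points for the strategy contrasts (assumed tier spreads up to ±15 points, constant risk difference, three equal tiers). It is about 8 points for a trend over an unordered amount test (assumed 30/33/36%, 1,000 men per tier). The more useful result is a prespecified answer to the incentive-size question in section 5.2. Nothing here shows bias, inflated type I error or a shortfall in the stated power.

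**What to change.** In Protocol 5.7.2:

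1. Keep the two overall strategy contrasts, lottery vs fixed and loss aversion vs fixed, but stratify each by randomised tier. Use a CMH test with a Mantel-Haenszel risk difference, or a regression with strategy and tier as main effects.
2. Test the amount hypothesis with a 1-df trend across the ordered tiers, stratified by strategy.
3. Report tier-specific strategy differences with confidence intervals, and a strategy-by-tier test, labelled as supportive only.

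If only two tiers are used, the same text applies, and the trend becomes a stratified comparison of the two amounts. The cost is a sentence or two in the analysis section and a few lines of code. Tier is assigned at randomisation and so known for every man; no extra data or participants are needed.

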### 5.7.3 Sample Size & Accrual

The trial will have about 3,000 total participants. About 1,000 participants will be randomized to each type of incentive strategy (fixed incentives, lottery-based incentives, loss aversion incentives). There will also be equal numbers of participants assigned to each of the incentive amounts that are chosen. The sample size has been chosen to ensure there is adequate power for the primary *and* secondary analyses. For the primary analyses, if we assume HTC uptake is as low as 30% with fixed incentives, the study will have >80% power to detect a difference ( $\alpha=0.05$ , two-sided) in HTC uptake as small as 6% between the novel incentive and fixed incentive groups. If HTC uptake is 40% with fixed incentives, the study will have >80% power to detect a difference in HTC uptake as small as 7% in each of the novel incentive arms. For secondary analyses, if we assume 40% HTC uptake with fixed incentives (N=400), and 50% with lottery (N=500), we will have >80% power to detect a difference of at least 6% in HIV prevalence between testers in novel and fixed incentive groups (assuming prevalence of 6% in the fixed incentive group).

## 6. HIV Treatment Incentives Trial

### 6.1 Recruitment & Enrollment of Study Participants

#### 6.1.1 Recruitment

Men and women who test HIV positive at HIV testing venues within the study communities will be recruited to enroll in the HIV Treatment Incentives Trial. Following post-test counseling at an HIV testing venue, study staff will describe the trial and proceed with obtaining written consent for enrollment from those who meet the eligibility criteria below. Persons who wish to consider enrolling in the trial at a later date will remain eligible for screening for enrollment in the HIV Treatment Incentives Trial, and receive information on how to contact study staff for enrollment at a later date.

#### 6.1.2 Consent Process

Study staff will review the informed consent form with recruited adults who meet the inclusion and exclusion criteria below, and answer any questions about study participation. HIV-infected adults who provide written informed consent and meet criteria for enrollment will proceed to randomization.

#### 6.1.3 Screening for Enrollment

##### 6.1.3.1 Inclusion Criteria

- (a) Aged  $\geq 18$  years;
- (b) Reside in one of the four selected study communities;
- (c) Positive result obtained from rapid HIV antibody test algorithm

##### 6.1.3.2 Exclusion Criteria

- (a) Intention to move away from the community in the next six months.

Eligible individuals who provide written consent to study enrollment will be administered a brief questionnaire before being randomized.

### 6.2 Randomization

Eligible participants will be randomized to one of two study arms: an incentive vs. a no incentive (control) arm. Study staff will follow a table of block-randomized numbers to determine which condition (incentive vs. no incentive) each participant receives.

All participants (in both trial arms) will be informed that the local health facility offers ART to all HIV-infected persons and that plasma viral load measurements can take place at either the health facility, their homes, or a convenient location of their choosing. Study staff will provide HIV viral load counseling to all participants, which will include education on what an HIV “viral load” measurement is, and how antiretroviral therapy impacts an HIV-infected person’s viral load. In both intervention and control arms, an unconditional cash transfer of up to US\$5 will be provided upon enrollment to facilitate linkage to or retention in care. In addition, all participants will be provided with a one-month supply of trimethoprim-sulfamethoxazole and undergo symptom screening for active TB, according to Ugandan Ministry of Health guidelines.

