### 4. Study Design

a. HIV Testing Incentives Trial (Aim 1): Randomized, controlled trial (RCT) of three types of incentive strategies (lottery-based, loss aversion-based, and fixed incentives) and multiple incentive amounts among adult male residents of rural Ugandan study communities. Eligible men will be randomized in an equal ratio to study groups.

b. HIV Treatment Incentives Trial (Aim 2): Randomized, controlled trial of a financial incentive strategy (with escalating incentive amounts for early treatment initiation and treatment maintenance vs. the no incentive standard of care) on the primary outcome of HIV virologic suppression (plasma HIV RNA  $<400$  copies/mL 6 months after randomization) among HIV-infected adult residents of rural Ugandan study communities. Eligible adults will be randomized in a 1:1 ratio.

c. Repeat HIV Testing Incentives (Aim 3 Pilot Trial): Randomized, controlled pilot trial of loss aversion vs. gain-framed incentive strategies vs. no incentive for the primary outcome of acceptability and feasibility of participation in a loss aversion strategy, to promote repeat HIV testing among HIV-negative, high-risk residents of rural Ugandan study communities. Eligible adults will be randomized to a control group, a gain-framed incentive group, or loss-aversion based group in a 1:1:3 ratio.

d. Repeat HIV Testing Incentives (Aim 3 Trial): Randomized, controlled trial of loss aversion (deposit contract) vs. gain-framed incentive strategies vs. no incentive (control) for the primary outcome of retesting for HIV 3- and 6-months following enrollment among HIV-negative, high-risk adults recruited from study sites in southwestern Uganda. Eligible adults will be randomized to the three groups (control, gain-framed and loss aversion incentive groups) in a 1:1:1 ratio.

e. Sustainability and Cost-Effectiveness (Aim 4):

- i. *Sustainability of incentives on HIV testing behavior*: Prospective study of HIV testing uptake at community HIV testing venues up to four years after HIV Testing Incentives RCT participants took part in the RCT.
- ii. *Cost-effectiveness*: We will measure the full resources and associated costs of implementing the incentive interventions for HIV testing using micro-costing (to quantify resources used and unit costs), and time and motion logs of study staff.

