### 8.2 Randomization

Eligible participants will be randomized to one of three main arms: 1) a loss-aversion incentive in which participants will be asked to voluntarily make a deposit contract that can be retrieved if they retest for HIV in the future or can be lost if they do not retest; 2) a standard gain-framed incentive arm in which participants will be offered an incentive for retesting for HIV in the future; and 3) a no incentive (control) arm in which participants will be encouraged to retest for HIV in the future, but no incentives will be provided.

Randomization will occur as follows: study staff will provide participants previously block-randomized scratch cards or envelopes to determine which condition each participant receives. Study staff and participants will not know what study condition an individual is randomized to until the participant scratches the card. Eligible adults will be randomized to the three groups in a 1:1:1 ratio.

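### Section 6.2 assigns Aim 2 arms from a block-randomised table followed by study staff and states no step that hides upcoming assignments

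*Protocol*

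**What the plan says.** Aim 2 is an open comparison of an incentive with no incentive. Protocol Section 4 gives the ratio: "Eligible adults will be randomized in a 1:1 ratio".

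- **Who recruits (6.1.1).** After post-test counselling, "study staff will describe the trial and proceed with obtaining written consent for enrollment from those who meet the eligibility criteria below". Deferred entry is allowed: "Persons who wish to consider enrolling in the trial at a later date will remain eligible for screening for enrollment".
- **Eligibility (6.1.3).** Inclusion needs adult age, residence and a positive test. The single exclusion is: "Intention to move away from the community in the next six months".
- **Order of steps (6.1.3.2).** "Eligible individuals who provide written consent to study enrollment will be administered a brief questionnaire before being randomized".
- **Allocation (6.2).** "Study staff will follow a table of block-randomized numbers to determine which condition (incentive vs. no incentive) each participant receives". Section 6 adds nothing on who holds the table or how later rows are kept from view.
- **Aim 3 pilot and trial (7.2 and 8.2).** Both use scratch cards or envelopes prepared in advance from a block-randomised list, and both state: "Study staff and participants will not know what study condition an individual is randomized to until the participant scratches the card".
- **Outcome and analysis (6.5.1, 6.6.2).** HIV RNA is measured at enrollment and at each follow-up time. The primary comparison of six-month suppression is a two-sided chi-square test or another appropriate method, and no baseline adjustment is named.

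**The concern.** Random order protects a comparison only if the person deciding on entry cannot know the next assignment. Section 6.2 gives the table to the same named role that recruits and consents, and states no safeguard. Holding randomisation until after consent and the questionnaire does not hide the next row.

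The strongest likely predictor of six-month suppression is suppression at entry. Aim 2 does not exclude people already on treatment, and 6.3 provides for participants whose baseline RNA is undetectable. Treatment status could emerge in post-test counselling, although the protocol does not say so. The incentive arm can earn about US$30 (5 + 10 + 15, Section 6.3), which is a conceivable motive for favouring some people. A laboratory outcome does not guard against selection at entry, and a larger sample does not shrink such a bias.

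The same protocol describes concealment for two sister studies, so the setting does not force the weaker method.

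**Working it through.** **1. The plan's own figure.** Section 6.6.3 gives about 400 adults (200 per arm), 50% suppression in the control arm, a 15-point difference, two-sided alpha 0.05 and power above 80%.

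- SE of the difference = √(0.50×0.50/200 + 0.65×0.35/200) = 0.049.
- Power = Φ(0.15/0.049 − 1.96) ≈ 0.87 with the unpooled SE, and 0.86 with the pooled SE under the null.

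The stated power reproduces. The point disputes no figure.

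**2. The sections side by side.**

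| | Aim 2 (6.1–6.2) | Aim 3 pilot and trial (7.2, 8.2) |
|---|---|---|
| Recruits and consents | Study staff | Study staff |
| Source of the arm | Block-randomised table followed by staff | Block-randomised scratch cards or envelopes |
| Statement that the arm is unknown beforehand | None | Yes, for staff and participants |

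**3. What a visible list would add.** If rows were visible, every upcoming arm would be known. With a hidden 1:1 list and guesses made only from past assignments, always naming the arm with more places left in the block:

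- block of 2: (0.5 + 1)/2 = 75% correct;
- block of 4: (0.5 + 2/3 + 2/3 + 1)/4 = 71%;
- blocks of 6 and 8: 68% and 67%, by simulation of 50,000 blocks each.

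The protocol gives no block size.

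**4. Scale if steering happened (illustration).** Every suppression rate by group and every imbalance here is assumed. Only the overall 50% comes from the plan. Shift δ = imbalance × (rate in likely suppressors − rate in others). With no true effect the SE is √(2×0.25/200) = 5.0 points, and the two-sided error rate is 1 − Φ(1.96 − δ/5.0) + Φ(−1.96 − δ/5.0), with δ in points.

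| Assumed rates (share of likely suppressors) | Imbalance 5 points: shift, error rate | Imbalance 10 points: shift, error rate |
|---|---|---|
| 90% vs 30% (1/3) | 3.0 points, 9% | 6.0 points, 22% |
| 90% vs 32.9% (30%) | 2.9 points, 9% | 5.7 points, 21% |
| 80% vs 40% (1/4) | 2.0 points, 7% | 4.0 points, 13% |

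Each row averages to 50%. For example, 0.30×0.90 + 0.70×0.329 = 0.50.

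**5. A yardstick.** With 30% suppressed at entry and perfect concealment, chance imbalance has SE √(2×0.3×0.7/200) = 4.6 points. A 5-point baseline imbalance is thus about one chance SE, so observing one would not by itself indicate steering.

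**The case against.** A reader might infer that the recruiter can see the next arm, or that Aim 2 allocation was in fact unconcealed. The protocol does not establish either. Study staff is its generic term for whoever does the work, and 6.2 does not say who holds the table or whether rows are covered. That one person both recruits and reads ahead is an inference from a shared role name.

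A reader might also take the later-date option and the exclusion for intention to move as levers for staff. Both are worded around the participant's own wish or stated plan, and the eligibility list is short. Nor does the protocol show that staff know baseline suppression at allocation, since RNA results come from phlebotomy.

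Nor is the difference from Aim 3 a contradiction. These are separate trials and may allocate differently.

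Finally, Section 3.1 refers in the past tense to communities where Aims 1 and 2 were carried out, so enrolment may be over and new cards of no use.

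These objections stand as limits. They rule out any claim of demonstrated bias, and they rule out telling the sponsor to declare that allocation was unconcealed. They do not supply a safeguard: 6.2 states a method that does not conceal by itself, in a protocol that elsewhere describes one that does.

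**Conclusion.** As written, Section 6.2 leaves Aim 2 without protection against selection bias at entry. The conclusion rests on three things in the text: one named role for recruiting, consenting and following the table; no concealment step anywhere in Section 6; and an explicit one in 7.2 and 8.2. It is an unprotected risk, with no steering shown, and its size cannot be derived from the protocol. The illustrative shifts of 2 to 3 points for a 5-point imbalance and 4 to 6 points for a 10-point imbalance depend wholly on assumed rates. They show only that moderate steering would matter against a 15-point planned effect with an SE of 4.9. No sample-size figure changes.

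**What to change.** **If any Aim 2 enrolment remains:** amend 6.2 to use the block-randomised scratch cards or envelopes of 7.2 and 8.2, sequentially numbered, and opened only once eligibility, consent and the questionnaire are complete.

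**If enrolment has finished:**

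- State in 6.2 and in the report who held the table and whether upcoming rows were hidden. If a concealed method was in fact used, correct 6.2 to describe it.
- Report baseline HIV RNA suppression by arm.
- Add an estimate of the six-month difference adjusted for baseline HIV RNA, specified before outcomes are examined by arm. Make it a sensitivity analysis if the primary analysis is already fixed. State that it corrects measured imbalance only, and not steering on traits such as motivation.

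**Cost:** a short amendment, card printing where enrolment continues, and one extra model. The RNA data are already collected at enrollment under 6.5.1, and 6.6.2 leaves room for another suitable method.
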